#### Specific secondary outcome assessments for the distal radius

Grip strength will be evaluated using a Jamar dynamometer (Sammons Preston Roylan, Bolingbrook IL, USA). The average value of three successive measurements will be calculated as a percentage of the contralateral, healthy side [28]. An impairment of muscle power is defined as a clearly lower average value for the injured leading hand compared to the opposite hand. If the injury involves the non-leading hand, the average value must be 50% lower than that for the opposite hand [29].

The Patient-Rated Wrist Evaluation questionnaire (PRWE) is a 15-item survey which allows patients to self-assess their levels of pain and disability in activities of daily living. It will be used as published [30] or in a translated validated version according to the guidelines of Beaton et al [31].

In a subset of patients, the bone volume/trabecular volume (BV/TV) ratio will be measured using high resolution peripheral quantitative computed tomography (Xtreme CT) (Scanco Medical AG, Brüttisellen, Switzerland) and compared with DXA measurements.

For the measurement of distal radius BMD, the XTreme CT will be calibrated with the aid of a reference phantom [European Forearm Phantom (EFP-02-45; QRM, Moehrendorf, Germany)] consisting of a series of various hydroxyapatite densities.

#### Specific secondary outcome assessments for the proximal humerus

The Constant-Murley score is a 100-point functional shoulder assessment tool in which higher scores reflect increased function. It combines four separate subscales focusing on subjective pain, function, objective clinician assessment of range of motion and strength. The score will be used as originally published [32,33].

The Shoulder Pain And Disability Index (SPADI) is a self-administered questionnaire that assesses the severity of pain and the degree of difficulty with various activities of daily living that require upper extremity use. It will be used as published or in its validated version [34]. As no Chinese (Cantonese) validated version of the SPADI exists, formal translation according to established guidelines [31,35,36] has been performed. The Chinese version has been approved by the developer and will be pretested in the present study in Hong Kong.

A CT based method for the measurement of BMD at the proximal humerus will be validated, and subsequently used to preoperatively determine BMD for the contralateral limb [37]. Briefly, simultaneous CT imaging of the contralateral proximal humerus with a European Forearm Phantom (EFP-02-45; QRM, Moehrendorf, Germany) is performed; the phantom is placed on the midthorax of the patient. After acquisition, the measured CT units (Hounsfield Units [HU]) of the user-defined ROI can then be quantified from the EFP-based calibration curve, resulting in definitive BMD values. This CT assessment of proximal humerus BMD will then be compared to the DXA measurements used to quantify BMD of the distal radius.

A summary of all outcome measures assessed during each study is presented in Figure 1.

**Figure 1 F1:**
[figure not shown]
**Flow chart of the study protocol**.

### Timing of outcome assessments

For both studies, patients will be followed from the day of initial treatment to one year thereafter. The follow-up includes initial hospitalisation (baseline) and follow-up visits at 6 weeks, 3 months and 12 months following surgery. At these follow-ups all outcomes except radiological data will be measured in the hospitals. Any unplanned follow-up visits resulting from the occurrence of a complication during the 12-month period will also be documented. Additional telephone interviews will take place at the 6-month postoperative period to obtain the patient self-rating PRWE, SPADI, and EuroQol5 questionnaire evaluations.

### Safety monitoring

Due to the investigational nature of the study to evaluate the association of local BMD with the occurrence of specific types of treatment complications, the entire reporting process of complications/adverse events (AE) is adapted such that the investigators are obligated to report all types of events, independent of being classified as a complication or an AE.

A complication is defined as any occurrence or deviation from the normal treatment or outcome, regardless of whether it has any relationship with the treatment or product under investigation.

All complications occurring at any time during the patient's postoperative follow-up period will be reported by the subject or observed by the investigator and documented in a separate complication form, whether or not the investigator concludes the event to be related to the treatment. The form will include the following information:

▪ type and date of event

▪ study name and the patient identification and treatment number

▪ investigator name and phone number

▪ name of the suspect medical product and the day of implantation

▪ a short description of the complication

▪ event seriousness and relation to study participation

▪ most likely causative factor

▪ event treatment

▪ event outcome and the relation (if any) of the event to the treatment procedure

### Sample size and statistical analysis

The primary objective of both studies is to assess BMD as a risk factor for the development of treatment complications. This objective will be analysed based on a nested case-control design. Using this statistical approach, the outcome variable is the occurrence of any complication and the exposure variable is the BMD measurement at the contralateral side. Cases include subjects reported with any bone and fracture related complication during the study duration of 12 months. Controls are subjects without any recorded complication. Thus, the main conceptual approach in this analysis is the difference in population BMD means between the cases and controls.

A two-way superiority hypothesis that the BMD is lower in cases compared to controls will be tested. The appropriate approach is to test the null hypothesis which states that the BMD is equal in cases and controls, i.e. H0: μcontrols = μcases or H0: μcontrols - μcases = 0, where controls and cases are the means of the two independent normal distributions. The alternative hypothesis is that BMD is different between the cases and the controls, i.e. H1: μcontrols ≠ μcases or H1: μcontrols - μcases ≠ 0. Rejection of the null hypothesis leads to the acceptance of the alternative hypothesis. The expected direction is that BMD is lower among the cases, which suggests the association between low BMD and the occurrence of complications. The expected ratio of cases versus controls is 15:85 for distal radius fractures and 30:70 for the proximal humerus. A standard deviation of 0.05 g/cm^2 ^for radius BMD measurements has been estimated [38]. With an expected BMD of 0.4 g/cm^2 ^at the radius and 200 subjects, the distal radius study has 85% power to detect a difference of -0.03 g/cm^2 ^in BMD at the wrist between the cases and the controls (two-way test). This corresponds to a Cohen effect size of 0.6, which indicates a medium clinical difference. With a power of 85%, a significance level of 0.05 (two-sided), an additional 10% in the number of subjects to compensate for any loss of power due to an adjustment for imbalance between the groups, and an estimated 10% loss to follow-up at the 1-year clinical examination, the distal radius and proximal humerus studies require 244 and 148 patients, respectively. Our sample size estimates are based on the following series of assumptions: 1) the proportion of cases in the patient population (i.e. % subjects with any complication); 2) the standard deviation of BMD at distal radius; and 3) the difference of μ_controls _- μ_cases_. Sample size estimates were performed using the Study East Version 4.0.1 (Cytel Statistical Software, Cambridge MA, USA).

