## Methods/design

### Study design

Both studies are designed as prospective, multicentre open cohort studies with a nested case-control design. Open cohorts do not select subjects according to the type of exposure variable but enrol all members of the population and determine subsequent exposure status. In this case, exposure (i.e. local BMD level) has already occurred, but is not a criterion for subject enrolment. The major advantage of this type of approach as compared to a classical case control design is that in addition to comparing the BMD in cases and controls, we can also obtain an estimate of the risk of experiencing a complication in the general population.

The studies will be conducted at several participating clinics from Austria, Germany, Switzerland, Italy, China, Singapore and the US; recruitment will take place at 11 hospitals for the distal radius and 9 for the proximal humerus studies (Table 1).

**Table 1 T1:** List of participating clinics

Clinic	Distal radius	Proximal humerus

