### Primary outcome measure

The primary aim of both studies is to evaluate if patients who experience bone/fracture or implant/surgery complications following surgical treatment with open reduction and a fixation plate (cases) have poorer bone quality (determined by local BMD) compared to control patients who do not experience a complication; hence, whether there is an association between poor bone mineral density and the risk of complication. Therefore, the main outcome involves documentation of the occurrence of at least one local bone quality related complication during 12 months of follow-up. The classification of complications complies with the previously defined system of AO Clinical Investigation and Documentation [19]. The qualifying events include those directly involving either the local bone and fracture or the implant and its surgical application. A detailed definition of these clinical and/or radiologically detectable events for the distal radius and proximal humerus are listed in Table 4 and 5, respectively.

**Table 4 T4:** Detailed list of categorised definitions for bone/fracture and implant/surgery complications located at the distal radius

Bone/fracture	
(Secondary) Loss of reduction = secondary fragment dislocation = redisplacement = loss of radial/ulnar length = dorsal angle change = dorsal or palmar shortening	Any change in intra-/extraarticular angles, radial/ulnar length or secondary fragment dislocation compared to the immediate postoperative measurements
	
Malunion	Healed fracture in deformity (e.g. varus/valgus, rotational malunion) as a consequence of loss of reduction
Malunion = residual extraarticular deformity = residual articular gap/step-off	Inadequate/insufficient anatomical reduction as a consequence of significant change of the postoperative position. Bone unites in abnormal position and/or alignment
	
Fracture impaction	Articular impaction of ≥ 1 mm
	
Delayed healing	Insufficient signs of healing (> 3 months)
	
Nonunion	Indiscernible signs of healing (> 6 months)
Refracture = secondary fracture	Fracture occurs at the same radial site with a load level otherwise tolerated by normal bone after the bone has solidly bridged
	
Functional deficit	As assessed with the functional scores of DASH, PRWE, ROM and grip strength

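### The control rule has no follow-up condition, so event-free patients lost before 12 months count as controls, although the sample size treats them as lost

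*Protocol article*

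**What the plan says.** All references are to the Protocol article.

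- **Primary outcome measure:** "the main outcome involves documentation of the occurrence of at least one local bone quality related complication during 12 months of follow-up". Tables 4 and 5 list the qualifying events. Some can be recognised only late: delayed healing at the radius after 3 months, nonunion at either site after 6 months, and refracture only once the bone has bridged.
- **Sample size and statistical analysis, cases:** "Cases include subjects reported with any bone and fracture related complication during the study duration of 12 months".
- **Same section, controls:** "Controls are subjects without any recorded complication". No length of follow-up is attached.
- **Same section, sample size:** an allowance is made for "an estimated 10% loss to follow-up at the 1-year clinical examination", giving 244 and 148 patients.
- **Study design:** the stated advantage over a classical case-control study is that "we can also obtain an estimate of the risk of experiencing a complication in the general population".
- **Timing of outcome assessments:** "follow-up visits at 6 weeks, 3 months and 12 months following surgery", plus a telephone interview at 6 months for patient-rated questionnaires.

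**The concern.** Case status is tied to a 12-month window, but control status needs only an empty complication record. A patient last seen at 6 weeks cannot be recorded with delayed healing or nonunion, yet meets the control definition as fully as one examined at 12 months. The sample size calculation, by contrast, gives such patients no information.

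Two results depend on which statement governs. The complication risk is understated if unobserved patients are treated as event-free, whether or not loss is related to BMD. The BMD comparison is diluted because some controls are unseen cases, and it can move further in either direction if patients who are lost have lower or higher BMD than other controls.

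**Working it through.** **Inputs from the article.** Case share p = 0.15 (radius) and 0.30 (humerus); SD 0.05 g/cm²; difference 0.03 g/cm²; two-sided 0.05; power 85%; loss 10%; N = 244 and 148. Power below uses the noncentral t with noncentrality d / (0.05·√(1/n_cases + 1/n_controls)).

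**1. The article's own figures.** Total N by the normal formula is (1.96 + 1.036)² × 0.05² / (0.03² × p(1−p)) = 195.6 and 118.8; by the noncentral t it is 198 and 121. The article uses 200 for the radius. Then 200 × 1.1/0.9 = 244.4 and 121 × 1.1/0.9 = 147.9, which match 244 and 148. The formula is not printed, but dividing by 0.9 for loss reproduces both totals.

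**2. Complication risk if lost patients count as event-free.** Let r be the risk in lost patients relative to the others, and u the share of their events never recorded (r and u are assumptions; u = 1 is the upper bound).

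True risk = 0.9p + 0.1pr. Reported risk = 0.9p + 0.1pr(1−u).

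| r | u | Radius: true → reported | Humerus: true → reported | Relative error |
|---|---|---|---|---|
| 1 | 0.5 | 15% → 14.25% | 30% → 28.5% | −5% |
| 1 | 1 | 15% → 13.5% | 30% → 27% | −10% |
| 2 | 0.5 | 16.5% → 15% | 33% → 30% | −9% |
| 2 | 1 | 16.5% → 13.5% | 33% → 27% | −18% |

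**3. BMD contrast if loss is unrelated to BMD beyond case status** (r = 1, u = 1). The share of controls who are unseen cases is 0.1p/(1 − 0.9p): 0.015/0.865 = 1.7% and 0.030/0.730 = 4.1%. The difference becomes 0.03 × (1 − share) = 0.0295 and 0.0288. With 32.9 cases against 211.1 controls, and 40.0 against 108.0, power is about 88% and 87%. With r = 2 the differences are 0.0290 and 0.0275, and power is about 87% and 84%. All of these are before the 10% adjustment allowance is used up.

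**4. BMD contrast if lost patients average x g/cm² below other controls** (assumption; an alternative to step 3, not an addition). Lost patients make up 24.4/211.1 = 11.6% of radius controls and 14.8/108.0 = 13.7% of humerus controls. Difference = 0.03 − share × x.

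| x | Radius difference, power | Humerus difference, power |
|---|---|---|
| 0 | 0.0300, 89% | 0.0300, 90% |
| 0.015 | 0.0283, 85% | 0.0279, 85% |
| 0.03 | 0.0265, 81% | 0.0259, 79% |
| −0.03 | 0.0335 (inflated) | 0.0341 (inflated) |

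**5. With lost patients left out of the comparison of means.** 244 × 0.9 = 219.6 and 148 × 0.9 = 133.2 patients remain. If loss is non-informative, the expected difference stays at 0.03 and power is about 88% to 89%, again before the adjustment allowance.

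**6. Why deletion does not repair the risk.** Take r = 1 with half of the lost patients' events recorded, keep those cases and delete the event-free losses. The crude risk is 0.1425/(0.1425 + 0.765) = 15.7% against a true 15%, and 0.285/(0.285 + 0.63) = 31.1% against 30%.

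**The case against.** The strongest reply is that the article never says lost patients are coded as controls. The control sentence is a summary that follows a case sentence bounded by 12 months, final classification is made after the 12-month period, and the loss allowance suggests that such patients were meant to drop out. The handling of incomplete follow-up is commonly left to a fuller document. This shows what the authors probably intended. It does not remove the problem, because the article does fix the definition of its primary comparison group, and a later document could give the intended meaning only by overriding it.

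The reply has more force on size, and these parts stand:

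- The 10% is loss by the 1-year examination, not early loss. Many of these patients may have attended the 6-week and 3-month visits, and primary malpositioning is already present at operation. The −10% and −18% figures are therefore upper bounds.
- The article gives no formula for the risk. Its two groups do not even cover the cohort, since a patient with only a soft tissue complication fits neither. The risk figures use all enrolled patients as denominator, which is an assumption here.
- A reader might infer that the primary BMD comparison is seriously biased or underpowered. The documents do not support that. Power of 81% and 79% needs everyone lost to average 0.03 g/cm² below the other controls, the whole assumed case-control gap. Half that deficit still gives the planned 85%.

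**Conclusion.** The point holds as a conflict between two statements in one section, with a moderate effect on the risk estimate and a small one on the primary contrast. Under the literal control rule and the article's own 10% loss, the complication risk is understated by about 5% to 10% relative at equal risk, depending on how many events were recorded before loss, and by at most 18% if the risk of lost patients is doubled. The BMD difference shrinks by 2% (radius) and 4% (humerus) at equal risk when every event in lost patients is unseen. It moves materially only if BMD among those lost differs from that of other controls, and then in either direction. The relative risk, the share of unseen events and the BMD deficit are assumptions; the article gives none of them. The wording should be corrected, but nothing here calls for a new design or a larger sample.

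**What to change.** 1. Keep the comparison of mean BMD as the primary analysis, since the studies are sized on it. Define a control as a patient with no qualifying complication **and** an observed 12-month status. State that patients without a recorded event whose follow-up is incomplete are neither cases nor controls in this comparison.
2. Estimate the complication risk from all enrolled patients as cumulative incidence at 12 months, with censoring at the last assessment and death as a competing event. Do not report a crude proportion after deleting event-free losses (step 6 of the working).
3. Add a supporting analysis that includes patients with incomplete follow-up: either a model of time to first qualifying complication on BMD, or a sensitivity analysis over plausible outcomes for those lost. This matters because, if low-BMD patients are lost more often, leaving them out raises the control mean and can exaggerate the contrast.

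**Cost.** Wording and one supporting analysis. The complication form already records the date of each event. There are slightly fewer controls, which the 10% loss allowance already covers. Events found on radiographs at widely spaced visits will carry dates that partly reflect visit timing, which is one reason to keep the time-to-event model in a supporting role.

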## Discussion

Although an association between local bone quality and implant anchorage has been proven in various in vitro settings, clinical evidence is still lacking [7]. Case reports as well as clinical experience suggest that fractures in osteoporotic patients are at higher risk of implant complication. Quantification of the problem is required in order to a) determine the size of the problem, b) provide numbers and characteristics for implant development, c) establish a basis for treatment decision-making, and d) support teaching in the field of geriatric fracture care. The proof of the hypothesised association is only possible in a controlled setting. Therefore, our study approach focuses on two major osteoporosis related indications. Distal radius fractures are regarded as sentinel fractures. Previous studies show high correlations between the degree of osteoporosis and radiological healing criteria [39,40], but surgical treatment with locked plates may have a positive impact on this correlation. For proximal humerus fractures, the use of locked plates does not seem to prevent all complications; rates of up to 40% are reported in the literature [41,42]. In this context, it is interesting to evaluate whether local bone quality is a significant contributing factor.

Although the study goals and methodology are novel, a few assumptions need to be made. Since local bone quality cannot be measured directly at the fracture site, remote sites have to be evaluated. Previous work has shown that the contralateral site serves as a better surrogate than ipsilateral locations in other areas [24]. Yet conditions such as post-stroke hemiparesis have an influence on these elements. Therefore, in the case of a proximal humerus fracture, BMD will be measured at the ipsilateral distal radius as well as at the contralateral proximal humerus. In the case of a distal radius fracture, only the contralateral side can be utilised to estimate BMD at the fracture site.

The latest concept of complication assessment is utilised for this study [19]. The main feature is that it distinguishes between local and general complications, with the former divided into further subcategories of bone/fracture, implant/surgery, and soft tissue associated complications. This should enable the investigator to establish causality. Overlapping between the categories may influence the assessment. The new feature of centralised radiograph and complication assessment will greatly help to improve data quality and may minimise investigator bias in the assessment of cases and controls.

Despite significant efforts to unify surgical care in both treatment arms, many confounding variables may influence the hypothesised association. Differences in the surgical approach, surgical skills, hospital infrastructure and postoperative rehabilitation may contribute to variability in the final result, thus influencing and possibly masking a bone related effect. Nevertheless, the study protocol adopts a real-world approach and therefore, represents current clinical practice rather than a theoretical framework.
